### Recruitments

The participants of the study will be recruited from consecutively admitted patients for hospital treatment at the University I Department of Psychiatry, Psychotherapy and Early Intervention, Child and Adolescent Psychiatry Unit in Lublin, Poland.

According to the Eating Disorders Therapy Program adopted by our Department, patients with AN have an adaptation period of up to three days. On the fourth day, patients will be informed in detail on the course of the study, all study procedures, potential risks, and the benefits of each intervention. A written document outlining the study will be provided to all participants. This document will include the objectives and rationale of the research, assurances of voluntary participation, the study schedule, potential hazards, the procedures for maintaining the confidentiality of personal data, and the participants’ right to discontinue participation in the study at any moment without the necessity to provide a justification. The next step involves obtaining written informed consent for participation in the study from the participant or participant and parent/legal guardian.

### Allocation

The patients included in the study will be randomly assigned to one of two subgroups, independently of examined variables, during the entry of the study: Active group - AG (tDCS group, n=25) and Sham group - SG (placebo group, n=25).

Eligible patients will be randomized in equal proportions between the AG and SG arm. A random sequence generator (Urbaniak GC, Plous S. Research Randomizer (Version 4.0) 2013) will be used to randomize active versus sham arms. The allocation to study groups will be performed by a researcher not involved in the stimulation and assessment of patients.

### Blinding

The researchers, participants, and their parents will be unaware of the group allocation as part of the blinding process. Moreover, data for each measure will be obtained by blinded experimenters and subsequently entered into secure data files to maintain confidentiality and protect the integrity of the study. The randomization will be performed using a random sequence generator and the results of allocation will be saved in a spreadsheet. The research assistant will generate randomization identification numbers for each participant based on the obtained data. The stimulation condition (duration, electric current, active or sham therapy) must be entered into the device to generate unique codes. The obtained number, together with the patient’s ID, will be written by the technical worker in an online spreadsheet. The study research coordinator will download the code from the prepared online sheet each time before the tDCS session and mark the used code.

## Data collection methods

To evaluate the efficacy of the intervention on the symptoms of patients with AN, the following changes will be determined:

1. Using paper-pencil questionnaires:

a) the severity of depression symptoms between V1 and V2 measurement (BDI total score/CDI2 total score);

b) the severity of symptoms of eating disorders and inappropriate eating behaviors (EAT-26 total score, QEB total score, EDE-Q 6.0 total score, FIVq total score);

c) neurocognitive functions between V1 and V2 measurement (total score: APT, ROCF, CTT-1, CTT-2, BVMT, VFT).

d) psychological measurements connected with dysfunctional metacognitive beliefs, other aspects related to thinking (such as reflectivity, impulsivity, rumination) and obsessive-compulsive symptoms, stress levels and assessment of early childhood injuries related to the experience of abuse, emotional, bodily, sexual, emotional, and physical neglect, and self-assessment of the appearance of one’s body between V1 and V2 measurement (total score: MCQ-A, RRQ, MTT, CY-BOCS, PSS-10; CTQ, ASRS),.

2. To evaluate the effect of the intervention on physiological parameters, the following changes will be measured:

a) In serum, from the baseline (V1) to the end of the stimulation (V2), levels of:

CBC, ferritin, TSH, FT3, FT4, electrolytes: phosphorus, magnesium and calcium, HPA axis biomarker: cortisol, markers of food intake regulation (plasma leptin and serum visfatin), neurotrophins (serum brain-derived neurotrophic factor: BDNF, nerve growth factor: NGF, neurotrophin 3 and 4.

Blood will be drawn by a qualified hospital staff member, and then a portion of it will be analyzed in the hospital laboratory, while another part will be frozen for conducting ELISA analyses at the level of neurotrophins, cortisol, and food intake regulators after the completion of the group collection.

b) Anthropometric data, from the baseline (V1) to the end of the study (V3):

Body weight will be measured, and body composition will be analyzed using the electrical bioimpedance method (BIA), Impedimed SFB7 BIS Research Device will be used. Anthropometric measurements will be carried out by a dietitian.

c) Brain activity, at the baseline (V1) and at the end of the stimulation (V2): EEG. The examination and analysis will be conducted by a qualified employee of the clinical neuropsychology laboratory.

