### Measures

To verify the effectiveness of both the active and sham tDCS stimulation methods, the following measures will be used:

I. For sociodemographic data: self-prepared personal questionnaire. The survey will cover personal data, medical history, information on menstruation, and used pharmacotherapy.

II. For psychological data:

The psychological examination consists of 14 tests using the paper-and-pencil method and is divided into 2 parts (the minimum interval between their administration is 4 hours, presented in the **Table 2**). During this time between examinations, patients were hospitalized in the ward. The psychological diagnosis will examine the following areas: neurocognitive functions (complex attention, executive functions, memory, language, social cognition), mood, obsessive-compulsive symptoms, and stress levels and assessment of early childhood injuries related to the experience of abuse, emotional, bodily, sexual, emotional, and physical neglect, and level of satisfaction with one’s own body. The first part includes the following tools: The Rey-Osterrieth complex figure test (ROCF), The Children’s Depression Inventory 2 (CDI-2)/the Beck Depression Inventory (BDI), The Yale-Brown Obsessive Compulsive Scale (CY-BOCS), The Color Connection Test (CTT1 and CTT2), The Benton Visual Retention Test (BVRT), The Perceived Stress Scale (PSS-10), The Childhood Trauma Questionnaire (CTQ) (30- 45 minutes); the second part includes: The Ruminance-Reflectivity Questionnaire (RRQ), The Attention and Perceptiveness Tests (APT), The Appearance Self-Rating Sheet (ASRS), The Verbal Fluency Test (VFT), The Metacognition Questionnaire (MCQ-A) (30- 45 minutes) measure for V1 and V2 respectively.

**Table 2 T2:** List of psychological tests performed on patients with AN.

Part 1	Part 2
1. The Rey-Osterrieth complex figure test 2. The Children’s Depression Inventory 2/Beck Depression Inventory 3. The Yale-Brown Obsessive Compulsive Scale 4. The Color Connection Test 5. The Benton Visual Retention Test 6. The Perceived Stress Scale 7. The Childhood Trauma Questionnaire	1. The Matching Familiar Figures Test 2. The Attention and Perceptiveness Tests 3. The Verbal Fluency Test 4. The Appearance Self-Rating Sheet 5. The Metacognition Questionnaire 6. The Ruminance-Reflectivity Questionnaire

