1) The Beck Depression Inventory (BDI) by Aaron Beck- It is a self-assessment tool that is helpful in screening the diagnosis of depression and measuring its severity (31). It consists of 21 multiple-choice questions. This tool will be used for adolescents who are over 18 years of age. The Polish adaptation was validated by Zawdzki, Popiel & Pragłowska. Cronbach’s alpha was 0.930 and 0.950, respectively (32);2) The Children’s Depression Inventory 2 (CDI2) by Maria Kovacs. A set of questionnaires is responsible for the self-reporting measurement of the severity of symptoms of depression in children and adolescents. It consists of 28 questions, the respondent chooses the answer containing the mode of functioning closest to his or her well-being. The filling time is 10-15 minutes. The test is intended for children aged 7-18 (33). The Polish adaptation was validated by Wrocławska-Warchala, Wujcik & Kovacs was used. Reliability for the general Cronbach’s α score is 0.840–0.870 (34);3) The Metacognition Questionnaire (MCQ-A) by Cartwright-Hatton, Mather, Illingworth, Brocki, Harrington, & Wells - is a reliable and valid instrument for assessing the severity of dysfunctional metacognitive beliefs in adolescents (aged 12-18) that affect their daily functioning (35). The first and second subscales measure “positive and negative beliefs about worry,” Subscale 3 measures “cognitive confidence,” and Subscale 4 measures “beliefs about superstition, punishment, and responsibility”. Finally, subscale 5 measures “cognitive self-consciousness,”. The test takes 10-15 minutes. The Polish adaptation were validated by Kajka & Kulik was used. Cronbach’s alpha reliability analysis for the adapted questionnaire was 0.874 (36);4) The Perceived Stress Scale (PSS-10) by Cohen, Kamarck & Mermelstein. Consists of 10 questions and is used to measure stress based on subjective feelings related to problems and personal events, behavior, and coping with stress (37). On average, completing the test takes up to 5 minutes. The questionnaire has age norms for youth 18 years and older. The Polish adaptation was validated by Juczyński i Ogińska-Bulik. Cronbach’s alpha reliability analysis for the adapted questionnaire was 0.860 (38);5) The Childhood Trauma Questionnaire (CTQ) by Bernstein, Fink, Handelsman & Foote. CTQ is used to assess early childhood injuries related to the experience of abuse, emotional, bodily, sexual, emotional and physical neglect. The questionnaire has age norms for adolescents (aged 12-17). Cronbach’s alpha reliability analysis for this questionnaire was 0.900 (39). The Polish translation was done by Murzyn (40);6) The Attention and Perceptiveness Tests (APT) version 6/9- Performing the test consists in drawing the given symbols - 6, 9 among other similar ones within three minutes. The questionnaire has age norms for youth from 14 to 18 and adults over 18 years of age. The reliability of this tool measured as temporal consistency (test-retest) is 0.790. On average, completing the test takes 3 minutes. The author of the tool is Ciechanowicz (41);7) The Rey-Osterrieth complex figure test (ROCF) was first designed by Rey and then standardized by Osterrieth. This is a neuropsychological test extensively used to investigate visuospatial constructional functions, visual graphic memory, and some aspects of planning and executive function. The questionnaire has age norms for children and adolescents from 8.6 years to 13.6 years. Cronbach’s alpha reliability analysis for this questionnaire was 0.761-0.793 (42). In the present study, participants first recreate the pattern patterns from the cards, then have a break to complete another questionnaire (CTT), and then recreate the patterns from memory after the break time (43);8) The Yale-Brown Obsessive Compulsive Scale (CY-BOCS) by Goodman, Price, Rasmussen, Mazure, Fleischmann, Hill, Heninger, & Charney is a scale designed to measure the severity and type of symptoms in people with obsessive-compulsive disorder (44). The respondents answer 10 questions about the occurrence of symptoms in the last week. The questionnaire has age norms for children and adolescents from 12 years to 16 years. The Polish adaptation was validated by Bryńska & Wolańczyk. Cronbach’s alpha reliability analysis for this questionnaire was 0.810 (45);9) The Colour Connection Test (CTT-1, CTT-2) by D’Elia, Satz, Uchiyama, & White. The Neuropsychological Point Matching Test measures attention, executive function, and psychomotor skills (28). It consists of connecting points with straight lines according to specific rules. The test takes 4 minutes. The Polish adaptation were validated by Łojek & Stańczak. The questionnaire has age norms for children and adolescents from 6 years to 80 years. Cronbach’s alpha reliability analysis for this questionnaire was 0.600-0.900 (46, 47);10) The Benton Visual Retention Test (BVRT) by Benton is used to test memory, visual perception and graphomotor skills. The examined person draws the presented patterns (10 pieces) from memory or redraws them, depending on the version and methods of the research carried out by the researcher. The questionnaire has age norms for children and adolescents from 8 years to 69 years (48). Testing one version takes about 5 minutes. The Polish adaptation was validated by Jaworowska, Bac & Stańczak. The analysis of reliability as the consistency of judges’ ratings was assessed as very high (0.900-0.970) (49);11) The Appearance Self-Rating Sheet (ASRS) - Sheet is a tool to measure the Assessment of 25 dimensions related to your body - (different parts of your body). The patient receives a visualization of the body figure on the drawing and evaluates its individual elements. The test allows you to assess the importance of appearance for patients, the assessment of satisfaction with one’s appearance, and the satisfaction index. The questionnaire has age norms for people aged 17-47. The authors of the test are Janowski, Staniewski & Jedynak. Cronbach’s alpha reliability analysis for this questionnaire was 0.719 (50).12) The Ruminance-Reflectivity Questionnaire (RRQ) by Trapnell & Campbell *i*s a tool used to measure the intensity of processes of rumination (and reflectivity) (51). The Polish adaptation of the tool consists of 12 questions, to which the respondent responds on a 5-point scale, where 1 means - I do not agree completely, and 5 - I agree completely. The questionnaire has age norms for people aged 20-50. Cronbach’s alpha reliability analysis for this questionnaire was 0.900-0.910. The author of the test is Radoń (52);13) The Verbal Fluency Test (VFT) by Thurstone allows for analyzing the number of spoken words beginning with the letter chosen. In the Polish version, the respondent has to enumerate as many words for the K letter as possible in 60 seconds. This is a clinical experimental test used in the diagnosis of both children and adults. Polish standards are for children aged 10-12. Reliability as temporal consistency of this tool is high, and it corresponds to a correlation coefficient of over 0.700. The Polish adaptation were validated by Borkowska, Sajewicz-Radke, Lipowska & Kalka (53);14) Matching Familiar Figures Test (MFF) by Kagan, Rosman, Day, Albert & Phillips is used to measure conceptual tempo, that is, the relative speed with which an individual makes decisions on complex tasks (see reflection – impulsivity). It consists of the fact that the examined person has a drawing presented, and then from among 6 pictures, he has to choose the one he saw previously. The researcher counts the time in which the decision was made (54). The Polish adaptation was validated by Matczak & Wujcik. The questionnaire has age norms for people aged 9-17. Reliability analysis for reaction time showed a high index (0.85 - 0.90) and a low index for the number of errors (0.400 - 0.580) (55).

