#### Secondary outcome measures

For the purpose of evaluating the effectiveness of tDCS in treating AN, a range of secondary outcome measures will also be utilized, defined as changes in: 1. anthropometric measurements (in this BMI), 2. brain bioelectric activity, 3. nutritional status, 4. mood, 5. neurocognitive functions (attention, memory, and some aspects of planning, verbal fluency, and another executive function), 6. psychological measurements connected with: dysfunctional metacognitive beliefs, other aspects related to thinking such as reflectivity, impulsivity, rumination, obsessive-compulsive symptoms, stress levels and assessment of early childhood injuries related to the experience of abuse, emotional, bodily, sexual, emotional, and physical neglect, and self-assessment of the appearance of one’s body, 7. selected biological markers related to stress, food intake, inflammation and neurotrophins.

As regards the neurophysiological measures, we expect that a series of the tDCS sessions will be associated with changes in three aspects: 1. reduction of lower frequencies (delta and theta) in the dominant frequency spectrogram accompanied with an increase in the power of alpha and beta frequencies, 2. modification of alpha anterior asymmetry patterns associated with affective functioning towards less right-hemisphere-oriented and more left-hemisphere oriented pattern, 3. changes in the strength and variability of functional connectivity, with particular alterations regarding alpha (increase) and beta (decrease) frequencies, what is associated with the ability to gain more relaxed and less tensive states recorded during resting-state condition. The neurophysiological examination will be conducted during the V1 and V2 meetings.

Secondary psychological outcome measures will be gathered during the initial assessment (V1) and V2, while nutritional data will be collected at V1, V2, and V3 after follow-up. Biological outcomes will be recorded at V1 and V2, with additional measurements of BMI and BIA analysis also at V3. Neurophysiological outcome measures will be obtained during V1 and V2.

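### The Childhood Trauma Questionnaire total score is set as a V1-V2 efficacy outcome, but a three-week change in it cannot be read as efficacy; collect it at baseline only (minor)

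*Protocol article*

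**What the plan says.** All references are to the protocol article.

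- **What the instrument measures.** Measures, part II, item 5: "CTQ is used to assess early childhood injuries related to the experience of abuse, emotional, bodily, sexual, emotional and physical neglect".
- **When it is given.** Measures, part II, and Table 2 place the CTQ in part 1 of the psychological battery, and the text on the two parts ends "measure for V1 and V2 respectively". Table 1 marks psychological assessments at V1 and V2 and makes no exception for the CTQ.
- **What it is used for.** Secondary outcome measures introduces "a range of secondary outcome measures will also be utilized, defined as changes in" a numbered list, and item 6 of that list includes "stress levels and assessment of early childhood injuries related to the experience of abuse". The same section adds: "Secondary psychological outcome measures will be gathered during the initial assessment (V1) and V2".
- **How the change is specified.** Data collection methods opens with "To evaluate the efficacy of the intervention on the symptoms of patients with AN, the following changes will be determined". Item 1(d) then names the scores: "between V1 and V2 measurement (total score: MCQ-A, RRQ, MTT, CY-BOCS, PSS-10; CTQ, ASRS".

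Nowhere is the CTQ limited to baseline or called a covariate, moderator or descriptor.

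**The concern.** A change outcome is useful only if the treatment could alter what it measures. Early-childhood abuse and neglect lie in the past when a participant is randomised, and three weeks of stimulation cannot alter them. The plan nevertheless lists the change in the CTQ score among the measures of efficacy on symptoms of anorexia nervosa.

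Three things are at stake, all modest. A significant result would have no meaning as efficacy, and a null result would say nothing about the treatment. The test occupies a place among the Bonferroni-corrected comparisons. Participants are also asked about abuse and neglect a second time, about three weeks after the first, for an answer that the trial cannot use.

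**Working it through.** The plan gives no figure for this point, so there is none to reproduce. The check is mainly a reading of the text, with two small calculations to show scale.

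**1. Is the CTQ really a repeated change outcome?** Four places bear on it.

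| Section | What it fixes |
|---|---|
| Measures, part II, and Table 2 | CTQ is in part 1 of the battery |
| Table 1 | Psychological assessments at V1 and V2, no exception |
| Secondary outcome measures | Childhood trauma is in a list of change outcomes, gathered at V1 and V2 |
| Data collection methods, item 1(d) | CTQ total score named, V1 to V2, under an efficacy purpose |

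The closing word of the timing phrase in Measures is loose and could suggest one part per visit. The other sections settle that both parts are given at both visits.

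**2. What can the change contain?** Write a participant's score as the true history plus a reporting component:

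- V1 score = T + e1
- V2 score = T + e2
- Change = (T + e2) − (T + e1) = e2 − e1

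T is fixed before randomisation and drops out. The difference between arms in mean change is therefore the difference in mean (e2 − e1), which is reporting only. Two cases follow.

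- If e1 and e2 are pure retest error, the expected difference between randomised arms is zero, and any significant result is a chance finding.
- If reporting depends on mood, and stimulation alters mood, the arms may differ. The difference then reflects recall or disclosure. Mood is already a secondary outcome, measured directly with the BDI or CDI-2.

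In neither case does the result measure efficacy on childhood trauma, nor is it a direct measure of symptoms of anorexia nervosa.

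**3. Cost in multiplicity (illustration only).** Statistical methods states a Bonferroni correction but not the family. Assume alpha = 0.05 and threshold = 0.05/m, with m counted from item 1 of Data collection methods:

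- 1(a) BDI or CDI-2, counted as one: 1
- 1(b) EAT-26, QEB, EDE-Q, FIVq: 4
- 1(c) six neurocognitive scores: 6
- 1(d) seven psychological scores, including the CTQ: 7
- Total: 1 + 4 + 6 + 7 = 18

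| Assumed family | With CTQ | Without CTQ |
|---|---|---|
| Item 1(d) only | 0.05/7 = 0.00714 | 0.05/6 = 0.00833 |
| All questionnaire scores | 0.05/18 = 0.00278 | 0.05/17 = 0.00294 |

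A family that also held the laboratory and EEG outcomes would show a smaller shift still.

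**4. Number of repeat administrations.** Fifty are to be included with 20% dropout allowed (Sample size calculation), so 50 × (1 − 0.20) = 40 are expected to complete and at most 50 would repeat the CTQ at V2.

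**The case against.** The strongest reply is that the CTQ is a self-report, so its score, unlike the events, can move. If stimulation improves mood, reporting may shift, and a blinded, randomised, sham-controlled comparison would estimate that shift fairly. This stands, and it rules out one tempting inference: that stimulation cannot change the CTQ score. The documents do not support that, since mood is a declared secondary outcome and the score depends on recall and disclosure. What survives is narrower: a shift in reporting is not efficacy, and the article states no aim of studying reporting.

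Other points for the plan also hold in part.

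- **False positives.** A reader might put the risk from this outcome at 5%. That would apply only without correction, and Statistical methods states a Bonferroni correction. The risk would also be the same for any other null secondary outcome.
- **Objectives.** That section does not name childhood trauma among the treatment effects, and a reader might infer that its listing elsewhere is a slip. The inference is weak, because the Objectives also leave out rumination and self-assessed appearance, which Secondary outcome measures includes.
- **Burden.** A reader might picture 50 minors. Eligibility runs from 13 to 25 years, the number of minors is not given, and the article reports neither a completion time for the CTQ nor any harm from repeating it. The burden is real but unquantified.
- **Value of a repeat.** A second administration could show retest stability or mood-dependent reporting. That value is not zero, but the plan states no use for it.

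An unseen analysis plan does not answer the point, which concerns what the article states and not something it leaves out.

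**Conclusion.** The concern holds as a minor point. As written, the plan gives the CTQ at V1 and V2 and treats the change in its total score as evidence on efficacy. That change can reflect only retest error or mood-dependent recall and disclosure, so neither a positive nor a null result would bear on efficacy.

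The conclusion rests on one assumption, taken from the article's own description: the CTQ asks about early childhood, so the history it records is the same at both visits. The multiplicity figures rest on an assumed alpha of 0.05 and an assumed family, and they show only that this cost is very small.

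A reader might go further and infer that the trial's efficacy conclusions are compromised or that a spurious CTQ effect will be claimed. The documents support neither. The EAT-26 primary outcome and the sample size are untouched, and no directional hypothesis about the CTQ is stated. The effect is confined to one secondary outcome and one avoidable repeat of a sensitive questionnaire.

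**What to change.** - In Measures, part II, and Table 1, state that the CTQ is administered at V1 only, and take it out of the V2 battery.
- Delete childhood trauma from item 6 of Secondary outcome measures, and the CTQ from item 1(d) of Data collection methods.
- Report the V1 total score by arm as a baseline characteristic. Label any moderator analysis exploratory; with about 40 completers it would have little precision.

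If the investigators want the repeat for its own sake, the article should state that aim and keep the result apart from the efficacy outcomes.

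The cost is a minor amendment. It removes one questionnaire from V2 and one test from the comparisons. All that is lost is retest or recall-stability data, which the protocol states no aim to use.
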